## Abstract

**Background:**

More effective methods are needed to implement evidence-based findings into practice. The Advancing Recovery Framework offers a multi-level approach to evidence-based practice implementation by aligning purchasing and regulatory policies at the payer level with organizational change strategies at the organizational level.

**Methods:**

The Advancing Recovery Buprenorphine Implementation Study is a cluster-randomized controlled trial designed to increase use of the evidence-based practice buprenorphine medication to treat opiate addiction. Ohio Alcohol, Drug Addiction, and Mental Health Services Boards (ADAMHS), who are payers, and their addiction treatment organizations were recruited for a trial to assess the effects of payer and treatment organization changes (using the Advancing Recovery Framework) versus treatment organization changes alone on the use of buprenorphine. A matched-pair randomization, based on county characteristics, was applied, resulting in seven county ADAMHS boards and twenty-five treatment organizations in each arm. Opioid dependent patients are nested within cluster (treatment organization), and treatment organization clusters are nested within ADAMHS county board. The primary outcome is the percentage of individuals with an opioid dependence diagnosis who use buprenorphine during the 24-month intervention period and the 12-month sustainability period. The trial is currently in the baseline data collection stage.

**Discussion:**

Although addiction treatment providers are under increasing pressure to implement evidence-based practices that have been proven to improve patient outcomes, adoption of these practices lags, compared to other areas of healthcare. Reasons frequently cited for the slow adoption of EBPs in addiction treatment include, regulatory issues, staff, or client resistance and lack of resources. Yet the way addiction treatment is funded, the payer’s role—has not received a lot of attention in research on EBP adoption.

This research is unique because it investigates the role of payers in evidence-based practice implementation using a randomized controlled design instead of case examples. The testing of the Advancing Recovery Framework is designed to broaden the understanding of the impact payers have on evidence-based practice (EBP) adoption.

**Trial registration:**

http://NCT01702142 (ClinicalTrials.gov registry, USA)

## Background

The use of evidence-based clinical practices in health care is suboptimal [1,2]. The addiction treatment field adopts evidence-based practices (EBPs) at an even lower rate than general health care [3-5]. For example, use of medication-assisted therapy for addiction disorders is not standard practice, despite the evidence that medication improves clinical, societal and financial outcomes through increased abstinence rates [6], reduced relapse rates [7], and reduced criminal costs [8]. A survey of 354 private addiction treatment centers reported that 34 percent of programs provided medication for opioid dependence and 24% used medication for treatment of alcohol dependence [9]. Within treatment programs that do offer medication, only 40% of the treatment plans for opioid dependence included medication [10].

Buprenorphine received Food and Drug Administration approval for treating opioid dependence in 2002 but remains underutilized. Less than one-fifth of patients with an opioid dependence diagnosis are offered buprenorphine [11,12]. Its adoption has been impeded by behavioral resistance, lack of or low reimbursement, insufficient access to personnel needed to prescribe the medication, licensure and contractual rules that prohibit the use of any pharmacotherapies in some settings, and insufficient organizational systems to encourage its use. Buprenorphine was selected as a candidate for EBP implementation and dissemination research because the broad set of behavioral and systemic barriers that limit its use incorporates factors that affect other EBPs with poor use rates.

Payer policy and organizational interventions can address barriers to the adoption of medication (and evidence-based practices more generally) [13,14]. Policy makers and local organizations collaborate to disseminate school reform, alternative energy use, and third-world agricultural practices [15,16]. Few trials in healthcare have tested the impact of aligning payer policy and treatment organization interventions to enhance implementation of treatment innovations [17]. However, from 2006 through 2010, NIATx (formerly the Network for the Improvement of Addiction Treatment), a process improvement research center based at the University of Wisconsin–Madison, conducted a demonstration project titled ‘Advancing Recovery: State and Treatment Organization Partnerships for Quality Addiction Care’. Funded by the Robert Wood Johnson Foundation, Advancing Recovery promoted the use of evidence-based practices such as medication-assisted treatment by building relationships between treatment organizations and the payers that fund their services. These partnerships made system changes to regulatory, clinical and administrative practices to increase the implementation of EBPs [18]. Advancing Recovery involved payer-treatment organization partnerships in 12 states, but was not a randomized controlled trial. The Advancing Recovery demonstration project did develop a framework for systems change to be tested in this randomized trial, calling it the Advancing Recovery Framework.

### Objectives

The primary research question is to determine if the Advancing Recovery Framework increases the use of buprenorphine in addiction treatment organizations. The secondary research question is to determine if county characteristics (*e.g*., percentage of opioid abusers, existing addiction treatment medication availability, and payment policy) and organizational characteristics (*e.g.*, organization size, access to physicians, number of nurses, percentage of clinicians with graduate degrees, and patient demographic characteristics) can moderate the delivery of buprenorphine.

## Methods

### Trial design

The participating ADAMHS boards have been randomized into two study conditions. In the Control Arm (Arm 1), participants will use the NIATx model for organizational change only. In Arm 2, participants will use the Advancing Recovery Framework that includes the payer intervention and NIATx models. Payers will not play a direct role in the control arm. The NIATx organizational change model (Figure 1) was chosen as the control condition because research exists that suggests organizational change models alone may be sufficient for EBP implementation [19,20]. A cluster randomized controlled design was used to study the effects that payers (or county ADAMHS boards) and treatment organizations have on buprenorphine adoption and also to control for ‘contamination’ across the treatment and control arms. A 1:1 allocation ratio of counties was utilized in the randomization.

**Figure 1 F1:**
[figure not shown]
The NIATx organizational change model.

### Participants

Ohio Alcohol, Drug Addiction and Mental Health Boards (ADAMHS) coordinate the public behavioral health system in Ohio. Each board covers one to five of Ohio’s 88 total counties and disperses Substance Abuse and Prevention Treatment (SAPT) block grant funds, as well as funds from local levies directed to addiction services. These Boards are responsible for 55% of addiction treatment services funding and often have responsibility for the quality and cost effectiveness of addiction treatment services within their jurisdictions [21]. The boards contract with provider organizations to deliver addiction and mental health treatment services. All 46 of Ohio’s ADAMHS boards were eligible for the study. The ADAMHS boards were recruited through an invitation from the Ohio Association of County Behavioral Health Authorities from May to September, 2012. The study team also actively recruited ADAMHS boards needed to meet the study’s matching criteria. A total of 14 boards representing 23 counties agreed to participate (Figure 2). Within each board jurisdiction, treatment agencies with 75 or more annual admission were invited to participate in the study. Fifty treatment agencies volunteered. Two to eight treatment agencies are participating per board.

**Figure 2 F2:**
[figure not shown]
Consort Diagram (Enrollment & Intervention Phases).

### Interventions

The Advancing Recovery Framework builds upon the multi-organizational learning collaborative method used in the NIATx 200 national trial to implement process improvement strategies in over 200 treatment organizations [22,23]. The Advancing Recovery Framework delivers technical assistance through learning sessions and coaching. Learning sessions are face-to-face meetings that occur once in the NIATx-only arm and three times in the Advancing Recovery arm to facilitate partnering between the ADAMHS boards and their treatment organizations. In these sessions, change teams from the ADAMHS board area (Arm 2 only) and each of the treatment organizations convene in face-to-face meetings to support and encourage each other. Outside experts offer advice on changes to make and ways to make them. Coaching assigns an expert in medication-assisted treatment adoption and process improvement to help the ADAMHS board and its treatment organizations make, sustain and spread buprenorphine adoption efforts. Coaches help the ADAMHS boards’ counties in Arm 2, and organizations in both arms think through key issues, broker relationships with other organizations, offer process improvement training, and suggest changes to make and how to do so. Participants in both arms receive coaching through monthly group teleconference calls, through e-mail, and at in-person learning sessions.

The payer intervention portion of the Advancing Recovery Framework has four phases: ‘Pre-Work for Leadership’ identifies the individuals who will lead and execute the change project; ‘Preparing the Change Leader & Team’ provides training in change management techniques; ‘Planning’ uses a five-lever policy analysis to catalog barriers to buprenorphine use and pilot tests potential tactics to remedy; and ‘Implementation’ takes tactics to apply from the planning phase, implements them, and focuses on sustaining the gains. During the learning sessions and monthly coach calls between the payer and treatment organizations, the payer has the opportunity to partner and collaborate with treatment organizations. Table 1 outlines the steps, tools, and training methods for each phase of the payer intervention model.

**Table 1 T1:** Payer intervention model of the advancing recovery framework (applied in Arm 2 only)

**Phase**^**1**^	**Steps**	**Tools**	**Training method(s)**
**Pre-work for Leadership**	To be completed as part of Executive Briefing by the Executive Director (or designee)	Executive sponsor (County Director) personal responsibilities checklist	Coach call to Executive Sponsor to review primer for Executive Sponsor
	1. Identify an Executive Sponsor for payer portion of the project		Change leader training on how to apply and interpret the 5 Levers Barriers Assessment
	2. Develop the strategic aim for buprenorphine adoption.		
	3. Select change leader and team members who are committed and make sure they have adequate time to participate in the project.		
**Preparing the Change Leader & Team**	4. Change Leader & Team Training on organizational and policy change techniques.	NIATx Workbook (Change Leader Training Guide – Administrative Version)	Provided in Learning Session 1 and reinforced by coaches throughout
**Planning (in conjunction with the treatment organization community)**	5. Conduct the 5 Levers Barriers Assessment. (Customer Impact, Financial & Purchasing, Regulatory & Policy, Operational, & Inter-organizational) to identify list of potential barriers to remove	5-Levers Policy-Barriers Assessment	Provided in Learning Session 1 and reinforced by coaches throughout
	6. Develop tactics to apply	Implementation charter form	
	7. Pilot test *tactics*		
**Implementation**	8. Develop list of *tactics* to implement (based on planning)	Implementation charter form	Change leader training in Learning Sessions on the implementation and sustainability process
	9. Assign a process owner, and timeline with deliverables for each *tactic*	Apply payer-based sustainability assessment form	
	10. Implement changes		
	11. Sustain gains		

The five levers described in the planning phase provide a mechanism for payers to identify systemic barriers to EBP use and promote change. The ‘customer impact analysis’ examines how the EBP benefits the customer, affects the number or type (*i.e.*, demographic) of customers involved in treatment, and which customers are needed to advocate for the change. A ‘financing and purchasing analysis’ determines how financing, reimbursement and payment provide incentives for EBP use. The ‘regulatory and policy analysis’ uncovers regulatory barriers. The ‘operations analysis’ assesses the training and skill-building payers and treatment organizations need for EBP implementation. Finally, an ‘inter-organizational analysis’ identifies what other organizations need to be involved to remove regulatory or financing barriers.

### Timeline

During project months 1 to 5, the study team will identify and recruit counties (through the Ohio Association of County Behavioral Health Authorities) and treatment organizations. In months 6 to 11, the study team will collect baseline data on buprenorphine use rates, conduct buprenorphine training workshops for treatment organizations, and update NIATx training materials to reflect the study conditions. In months 12 to 36, the study team will implement the study arm interventions and collect outcome data. During months 37 to 50, the study team will collect quantitative data on the sustainability of the changes. Data analysis, publication development, and dissemination of findings will occur at several points, but primarily during months 51 to 60.

### Sample size

To determine sample size, we fit a linear mixed-effects model to the monthly results for the performance measure of percent opioid dependent patients receiving buprenorphine from each of the participating organizations and estimate the ‘payer-treatment organization’ effect. A mixed-effect model was selected instead of conventional regression models because, first, the mean outcomes for a given treatment organization are expected to be correlated from month to month. A mixed-effect model allows for auto-correlated error terms. Second, a number of unobservable treatment organization characteristics are likely to influence the key measures. Random effects at the treatment organization level can be employed within the mixed-effect model to capture the correlation introduced by such characteristics. Proper reflection of auto-correlation and random effects allows for more reliable estimates of the fixed effects, starting in months 6 to 11 (for baseline), then during months 12 to 36 (intervention stage), and through months 37 to 50 (follow-up stage). The power of the study design is determined by the anticipated standardized effect size based on effects experienced in the Advancing Recovery pilot project. The Advancing Recovery pilot data found that the payer-treatment organization intervention increased buprenorphine use rates from 6% to 43%, with an estimated standard deviation of 23.5% based on a sample size of 1,016. This yields an effect size of 0.935. Intraclass correlation (ICC) among counties affects the power of cluster-randomized trials [24]. An estimate of ICC is around 0.05. For this study, a dropout rate of 20% is being proposed, giving a total of 40 organizations available for analysis. With a total of 40 treatment organizations, each with an average of 91 patients, the study will achieve at least a power of 0.82 with a one-tailed type I error rate of 0.05. Power and sample size calculations were performed using Optimal Design Software by Raudenbush (Version 3.01) [25]*.*

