Ohio was selected as a research site because it was considered to be a representative governmental healthcare environment to test this implementation model. A total of 34% of the states in the United States have county or region boards to distribute SAPT block grant funds. Each Ohio ADAMHS board represents a unique payer environment. The state has a mix of urban and rural counties. Within these counties, buprenorphine use varies from 7% to 58%. Limitations could be present due to the research environment. This trial addresses governmental payers securing healthcare services. Governmental healthcare is a considerable enterprise, where an effective framework for evidence-based practice implementation could prove to be extremely helpful. While this trial may not be generalizable to governmental payers for other community services, the Advancing Recovery framework could give these sectors interventions to consider in their efforts to improve services.

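### The sample-size paragraph does not form one calculation: 0.935 does not use the stated SD, the stated inputs give power near 1.00 rather than 0.82, and the effect is a pilot rise, not the contrast with NIATx alone

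*Protocol article*

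**What the plan says.** The Sample size section plans for a linear mixed-effects model on monthly organization-level percentages. Its planning effect comes from the Advancing Recovery pilot, which "increased buprenorphine use rates from 6% to 43%, with an estimated standard deviation of 23.5% based on a sample size of 1,016". The next sentence reads: "This yields an effect size of 0.935". On clustering it says "An estimate of ICC is around 0.05", described as applying among counties. On attrition it says "a dropout rate of 20% is being proposed, giving a total of 40 organizations available for analysis". From 40 organizations averaging 91 patients each, it claims power of at least 0.82 at a one-tailed type I error of 0.05.

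Three other places bear on the effect size:

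- The Background says that the pilot was not a randomized controlled trial.
- The Trial design section makes the control arm an active one (the NIATx organizational change model), on the ground that "research exists that suggests organizational change models alone may be sufficient for EBP implementation".
- The Discussion says of Ohio: "Within these counties, buprenorphine use varies from 7% to 58" per cent.

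No expected rate for the control arm is given.

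**The concern.** A reader who follows the printed steps cannot get from the rates and SD to 0.935, nor from 0.935 and the cluster inputs to 0.82. The quantity being planned for is also not the one the trial estimates. The pilot rise reflects payer and organizational change together, while the trial isolates what the payer component adds to NIATx.

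This paragraph is the article's only justification of size. As it stands, readers would take the trial to be sized for a very large between-arm effect. They could then read a null result as ruling out a worthwhile payer effect, when the paragraph does not show how well a realistic increment would be detected.

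**Working it through.** **Inputs.** From the Sample size section: rates 6% and 43%, SD 23.5%, effect size 0.935, ICC 0.05, 40 organizations, 91 patients per organization, one-tailed alpha 0.05, power at least 0.82. From the Abstract: seven boards per arm, so 14 randomized boards.

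**Step 1: the effect size.**

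- Difference over the stated SD: (43 − 6) / 23.5 = 1.574.
- Cohen's h: 2·asin(√0.43) − 2·asin(√0.06) = 1.4303 − 0.4949 = 0.9354.

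The second route reproduces 0.935, and the SD plays no part in it. An arcsine difference between two proportions is not the standardized mean difference suited to a linear mixed model on organization percentages, which is the model the section describes.

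**Step 2: the power, from the stated inputs.** For J clusters of m patients in two equal arms, the variance of the standardized difference is 4·[ICC + (1 − ICC)/m] / J. Power comes from the noncentral t distribution with J − 2 degrees of freedom.

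- Variance: 4 × (0.05 + 0.95/91) / 40 = 0.00604, so the standard error is 0.0777.
- Noncentrality at 0.935: 0.935 / 0.0777 = 12.0.
- One-tailed power with 38 df: 1.00 to three decimals.
- Effect at which one-tailed power is 0.82: about 0.20.

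**Step 3: can 0.82 be reached from 0.935 another way?** Yes. Take the 40 organizations as independent single observations, with variance 4/40 = 0.10 and noncentrality 0.935 / 0.316 = 2.96 on 38 df. Two-sided power at 0.05 is then 0.8216. The one-tailed version gives 0.896. The matching route therefore needs a two-sided test, no ICC and no cluster size, all of which contradict the text. It also treats organizations as independent although boards were randomized.

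**Step 4: what the increment over NIATx might be.** The documents give no control-arm rate, so the shares below are assumptions, as are placing the ICC of 0.05 at board level and using h as the standardized effect. Patients per board: 40 × 91 / 14 = 260. Variance: 4 × (0.05 + 0.95/260) / 14 = 0.01533, so the standard error is 0.124, with 12 df.

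| Assumed share of pilot gain delivered by NIATx alone | Control vs framework | h | Power, one-tailed | Power, two-sided |
|---|---|---|---|---|
| Half | 6 + 18.5 = 24.5% vs 43% | 0.39 | 0.91 | 0.83 |
| Three quarters | 6 + 27.75 = 33.75% vs 43% | 0.19 | 0.42 | 0.29 |

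On the same assumptions, the effect detectable with 0.82 one-tailed power is about 0.34. With the 40 organizations as clusters (Step 2) it is about 0.20.

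**The case against.** Several points on the other side stand.

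- **The number 0.935 is a correct index.** It is Cohen's h for the two stated rates. A reader might infer from 1.57 against 0.935 that the effect size is numerically wrong by a large margin. The documents do not support that, because these are different indices. The defect is that the index is unnamed and the SD is offered as an input when it is not one. The gap also makes no difference to power under the stated inputs, which is about 1.00 at either value.
- **0.82 can be reached from 0.935.** A reader might infer that effect size and power must come from unrelated calculations. Step 3 shows otherwise: it may be one calculation, misdescribed. What remains is that the printed inputs do not give the printed power.
- **The text says at least 0.82.** Power near 1.00 does not literally contradict that, but 0.82 is then uninformative as a summary of the design.
- **The trial may still be adequately powered.** If NIATx delivers half the pilot gain, board-level power is at or above 0.82. The documents do not show that the trial is underpowered.
- **Baseline and control.** The Trial design section says only that organizational change may be sufficient, not that it is expected to raise use by any amount. The 7% to 58% figure is a range without a mean. It shows that at least one county exceeds 43%, but not that the average Ohio baseline differs from the pilot's.

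It can also be said that recruitment is complete, so the sample is fixed. That limits the practical consequence, but it does not make the stated derivation right.

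**Conclusion.** The point holds in three parts.

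1. The stated derivation is wrong: 6%, 43% and SD 23.5% give 1.57 as a difference over SD, whereas 0.935 is an arcsine index that ignores the SD.
2. The stated inputs give power of about 1.00, not 0.82. This rests on the standard two-level formula with organizations as clusters.
3. The planning effect is a rise over time under the full framework, in a project that was not a randomized controlled trial, applied to a contrast with an active comparator. It probably overstates the between-arm effect. By how much cannot be determined from the documents.

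Part 3 matters most for interpretation. With 14 boards and an assumed board ICC of 0.05, one-tailed power runs from about 0.91 to 0.42 across the two assumed shares, so the adequacy of the sample depends on an increment the article never states.

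**What to change.** Rewrite the sample-size paragraph:

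- Remove the step from the SD of 23.5% to 0.935, and name the effect metric used (difference in proportions, arcsine h, or a standardized mean difference that suits the model).
- State the increment over NIATx alone that the trial is meant to detect, with the assumed control-arm rate and its basis in Ohio baseline data.
- Report power, or the detectable effect, from one calculation in which effect size, ICC, number of clusters, sidedness and power belong together, with the 14 randomized boards as the top-level unit. Say at which level the ICC applies.
- Keep the pilot rise as background only.

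The cost is a paragraph and a fresh calculation. The headline planning effect becomes smaller. Recruitment, the interventions and data collection do not change. At the time of the article baseline collection had only just begun, so the correction can precede any outcome analysis.

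### The stated power of 0.82 does not follow from its own inputs, and it is not set at the level of the 14 boards that were randomized

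*Protocol article*

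**What the plan says.** The Trial design section of the Protocol article makes the board the randomized unit: "The participating ADAMHS boards have been randomized into two study conditions". Participants gives 14 boards, Randomization & implementation gives seven matched pairs of boards, and the Abstract describes the allocation as "resulting in seven county ADAMHS boards and twenty-five treatment organizations in each arm".

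The Sample size section works with other units. It takes 20% dropout from the 50 organizations to reach 40 and states: "With a total of 40 treatment organizations, each with an average of 91 patients, the study will achieve at least a power of 0.82". The test is one-sided at the 5% level. Its other inputs are:
- a pilot result that "increased buprenorphine use rates from 6% to 43%, with an estimated standard deviation of 23.5% based on a sample size of 1,016", followed by "This yields an effect size of 0.935";
- an ICC of about 0.05, introduced by the sentence "Intraclass correlation (ICC) among counties affects the power of cluster-randomized trials".

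The section mentions random effects only for organizations. It uses neither the number of boards nor the pairing.

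Three other places bear on the unit. The Abstract and Data analysis call the treatment organization the cluster. Data analysis calls the board a site and describes a multi-site cluster randomization. Randomization & implementation says that organizations were assigned within the board pairs. Data analysis also plans random effects for both board and organization.

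**The concern.** The payer intervention acts on the board, so all organizations under one board share one arm and one payer. Variation between boards then enters the arm comparison in full, and the test of arm has at most 12 degrees of freedom (14 boards minus 2), or 6 if the seven pairs are kept. A calculation on 40 independent organizations would use 38 degrees of freedom and too small a standard error. Attaching an ICC described as among counties to organization-sized units adds to the doubt about level.

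At stake is what a null result would mean. The comparator is itself an organizational change programme that Trial design says may be enough for implementation. The payer effect in this trial could therefore be much smaller than the pilot's rise from 6% to 43%. At smaller effects, the choice of unit decides the power.

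**Working it through.** **Inputs.** From Sample size: J = 40 organizations, m = 91 patients each, ICC = 0.05, d = 0.935, one-tailed 0.05. From Participants and Randomization & implementation: 14 boards, 7 pairs. Derived: 40 × 91 = 3,640 patients; 3,640/14 = 260 patients per board; 40/14 = 2.857 organizations per board.

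**Formula.** SE = sqrt(4 × [ICC + (1 − ICC)/m] / J). Power comes from the noncentral t distribution with noncentrality d/SE.

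**Step 1: the plan's own figure.**
- 40 clusters: SE = sqrt(4 × [0.05 + 0.95/91]/40) = 0.0777. Noncentrality is 0.935/0.0777 = 12.0 on 38 df, and power is about 1.00.
- 14 boards: SE = sqrt(4 × [0.05 + 0.95/260]/14) = 0.1238. Noncentrality is 0.935/0.1238 = 7.55, and power is above 0.99 on 12 or 6 df.

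Neither gives 0.82. With 14 boards, the ICC would have to be about 0.41 (12 df) or 0.36 (6 df) before power at 0.935 fell to 0.82.

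**Step 2: the effect size.** (43 − 6)/23.5 = 37/23.5 = 1.574, not 0.935. The arcsine difference is 2·asin(√0.43) − 2·asin(√0.06) = 1.4303 − 0.4949 = 0.9354. That matches 0.935 but makes no use of the standard deviation quoted just before it.

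**Step 3: readings that come near 0.82 at d = 0.935.**

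| Reading | Power |
|---|---|
| 40 organizations as single independent observations, one-tailed, 38 df | 0.896 |
| The same, two-sided | 0.822 |
| 40 organizations as observations nested in 14 boards, board ICC 0.05, one-tailed | 0.846 (12 df), 0.802 (6 df) |
| The same, two-sided | 0.738 (12 df), 0.657 (6 df) |

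The closest match, 0.822, contradicts the stated one-tailed test. The independent-observation rows use neither the ICC nor the 91 patients. The nested rows use the ICC at board level but not the 91 patients.

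**Step 4: sensitivity by unit.** Standardized effect detectable with power 0.82 at ICC 0.05:

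| Unit | One-tailed | Two-sided |
|---|---|---|
| 40 organizations of 91, 38 df | 0.203 | 0.229 |
| 14 boards of 260, 12 df | 0.337 | 0.388 |
| 14 boards of 260, 6 df | 0.360 | 0.428 |

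One-tailed, the board-level value is 0.337/0.203 = 1.66 to 0.360/0.203 = 1.77 times the organization-level one.

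**Step 5: both levels of clustering.** SE = sqrt(4 × [rb + ro/2.857 + (1 − rb − ro)/260]/14), where rb is the board ICC and ro the organization-within-board ICC. Here ro = 0.05 is assumed, as are the values of rb other than 0.05.

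| rb | SE | Detectable, one-tailed (12, 6 df) | Two-sided (12, 6 df) |
|---|---|---|---|
| 0.02 | 0.108 | 0.29, 0.32 | 0.34, 0.38 |
| 0.05 | 0.142 | 0.39, 0.41 | 0.45, 0.49 |
| 0.10 | 0.186 | 0.51, 0.54 | 0.58, 0.64 |

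At d = 0.935, power stays above 0.99 in all three rows.

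**The case against.** The strongest reply is that nothing here shows 0.82 to be too high. A reader might infer that the stated power is overstated, or that the same inputs at board level give about half of it. The document does not support either inference. Its stated effect is 0.935, at which 14 boards still give power above 0.99 with ICC 0.05. Power of 0.46 or 0.42 with 14 boards appears only at an effect of about 0.20, a value obtained by solving backwards from 0.82 and found nowhere in the article. This part of the reply stands.

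Second, the section refers to an ICC among counties and never says that the 40 organizations were the randomized or independent units. The nested reading with board ICC 0.05 gives 0.80 to 0.85, so the figure might already allow for county clustering. That possibility stands, but the section does not state it and that reading would leave the 91 patients unused. Against it, the Abstract and Data analysis do call the organization the cluster.

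Third, the planned model already has a random effect for board, so the defect lies in the planning paragraph and not in the analysis of arm. This stands and limits the severity.

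Fourth, one-tailed testing is openly stated and fits a directional question. It is a choice, not an error; the two-sided figure is useful beside it.

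**Conclusion.** The point holds in a limited form. The power of 0.82 is not reproduced by the inputs printed with it, the effect size does not follow from the printed standard deviation, and the calculation leaves out the 14 boards and seven pairs. Whether the figure is too high cannot be determined. At d = 0.935 and ICC 0.05 it is not, since power exceeds 0.99 at either level.

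The loss of sensitivity is conditional. If the 40 organizations were taken as independent clusters, the effect detectable with 0.82 power is about 0.20, when the randomized units support 0.34 to 0.36 at the same ICC. The step 4 comparison assumes equal board sizes and no separate organization-level clustering. None of the calculations models the monthly repeated measures, the baseline data, any gain from matching, or the spread of two to eight organizations per board. The organization ICC and the wider board ICC range are assumptions.

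This is worth correcting before results are read against the figure, but it does not threaten the planned analysis.

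**What to change.** Replace the power statement in Sample size with a calculation that:
- takes 14 boards in seven pairs as the randomized units, with 12 df, or 6 df if pairs are kept in the analysis;
- gives separate ICCs for board and for organization within board, over a range labelled as an assumption, such as board ICC 0.02 to 0.10;
- states the scale of the effect size and derives it, dropping either the standard deviation or the 0.935 if they do not belong together;
- reports the detectable effect at the stated one-tailed 0.05, with the two-sided figure beside it;
- allows for loss of a whole board or pair as well as 20% of organizations.

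Reconcile Trial design, Randomization & implementation and Data analysis on whether boards or organizations were assigned, and on whether the multi-site description fits a design in which each board lies wholly in one arm.

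The cost is one rerun and one rewritten paragraph, plus the wording on the unit assigned. The stated sensitivity may become less favourable. No new recruitment is needed.
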